## Abstract

**Introduction:**

The COVID-19 pandemic underlined that guidelines and recommendations must be made more accessible and more understandable to the general public to improve health outcomes. The objective of this study is to evaluate, quantify, and compare the public’s understanding, usability, satisfaction, intention to implement, and preference for different ways of presenting COVID-19 health recommendations derived from the COVID-19 Living Map of Recommendations and Gateway to Contextualization (RecMap).

**Methods and analysis:**

This is a protocol for a multi-method study. Through an online survey, we will conduct pragmatic allocation-concealed, blinded superiority randomized controlled trials (RCTs) in three populations to test alternative formats of presenting health recommendations: adults, parents, and youth, with at least 240 participants in each population. Prior to initiating the RCT, our interventions will have been refined with relevant stakeholder input. The intervention arm will receive a plain language recommendation (PLR) format while the control arm will receive the corresponding original recommendation format as originally published by the guideline organizations (standard language version). Our primary outcome is understanding, and our secondary outcomes are accessibility and usability, satisfaction, intended behavior, and preference for the recommendation formats. Each population’s results will be analyzed separately. However, we are planning a meta-analysis of the results across populations. At the end of each survey, participants will be invited to participate in an optional one-on-one, virtual semi-structured interview to explore their user experience. All interviews will be transcribed and analyzed using the principles of thematic analysis and a hybrid inductive and deductive approach.

**Ethics and dissemination:**

Through Clinical Trials Ontario, the Hamilton Integrated Research Ethics Board has reviewed and approved this protocol (Project ID: 3856). The University of Alberta has approved the parent portion of the trial (Project ID:00114894). Findings from this study will be disseminated through open-access publications in peer-reviewed journals and using social media.

**Trial registration:**

Clinicaltrials.gov NCT05358990. Registered on May 3, 2022

**Supplementary Information:**

The online version contains supplementary material available at 10.1186/s13063-023-07067-9.

## Strengths and limitations of this study

We are following a multi-method approach: randomized controlled trials and qualitative interviews. The qualitative results will supplement and help explain our quantitative findings.This protocol is reported in accordance with the Standard Protocol Items: Recommendations for Interventional Trials (SPIRIT), which enhances transparency and completeness. The trials use previously validated outcomes from similar trials. This will strengthen the credibility of our results.Our study is testing an optimized plain language recommendation format, which makes our intervention relevant to our stakeholder groups, and is recruiting internationally, which ensures the inclusion of a diverse population. Recruitment will take place online using social media, and data will be collected using an online survey. This allows for self-selection and limits accessibility to those who have no or limited digital access, which in turn limits generalizability.While the recommendations are offered in multiple languages through the RecMap, the study is only testing English plain language recommendation summaries.

## Introduction

As health practitioners, policymakers, and the public are inundated with information, misinformation, and health recommendations about COVID-19, we have built a unique repository of trustworthy COVID-19 recommendations with funding from the Canadian Institutes of Health Research (CIHR) (covid19.recmap.org). The overarching goal of this COVID-19 RecMap effort is to identify all COVID-19 guidelines, assess their credibility and trustworthiness, and make their recommendations available and understandable to various stakeholder groups [1].

To enhance the understanding of health recommendations by the public, we developed a multi-stakeholder process to draft, edit, and publish plain language recommendations (PLRs) [2]. Until now, plain language versions of recommendations have been poorly explored, and our work on the RecMap indicates an absence of this critical knowledge mobilization tool for the general public, including youth, adults, and parents [3]. Existing trials on tailored recommendations presentations have been small and predated recent guidance on how to present guideline recommendations, targeted health professionals, or did not target the general public [4–7]. For example, a small trial with 84 mental health service users suggested an improved intention to follow recommendations when written in plain language [6]. Trial data also exists on specific aspects related to health information, like comparing alternative ways of presenting numerical or statistical information and formats of information sharing [4, 8–10]. However, trustworthy and comprehensive PLRs may need to include the clinical or public health background related to the topic, conflicts of interest, available research evidence, judgments that are made, the rationale for a recommendation, the actual recommendation, and implementation considerations. As addressed in Evidence to Decision (EtD) frameworks, these facets are deemed essential to inform decision-making and are used widely by various organizations [11–14].

A trial is necessary to empirically show that PLRs convey the intended messages from guidelines to broader populations and not only to the selected user groups that usually participate in ours and others’ research. Understanding and interpreting recommendations correctly are the essential prerequisites for the general public to become effective self-managers of their health and to ultimately optimize behaviors and related health outcomes [15]. Creating health information for the public that is accessible, reliable, and understandable is critical to scale science and evidence-based guidelines, which is especially important during the COVID-19 pandemic. We plan to undertake this trial, given the paucity of empirical evidence to guide our team and guideline developers as to how to best present PLRs and EtD facets to the public, which are critical to support their informed decision-making. This protocol describes the trials and details of the three leading trial sites.

## Objectives

The objective of this study is to compare end-users’ (youth, parents, and adult populations) understanding, accessibility and usability, satisfaction, intention to implement, and preference for COVID-19 recommendations when presented as plain language recommendation summaries (PLRs) versus standard language versions (SLVs). We hypothesize that there will be a difference in understanding of information between the two formats. We also aim to understand the reasons for their choices through our linked qualitative research.

## Methods

We will follow a multi-methods approach: randomized controlled trials (RCTs) with qualitative interviews among a subset of participants. The trials are pragmatic allocation-concealed, blinded superiority RCTs with at least 240 participants in each population (parents, adult, and youth). The trials were preceded by preparatory engagement work with Canadian youth advisors, a Canadian parent advisory group, and an international adult Cochrane Consumer group, herein referred to as stakeholder groups. The youth site’s preparatory engagement work was co-developed and implemented by two youth partners ([name]) in collaboration with LS, to ensure meaningful engagement efforts were embedded into the research process. We gathered input from stakeholders on COVID-19 priority topics and PLR content and format. Input from stakeholders helped us refine the PLR format to be evaluated with each population in the trial.

We will conduct qualitative interviews with a subset of the participants who completed the trials to help contextualize the digital user experience and understand the results of the trial.

Any amendments to this protocol will be made available via medRxiv.

### Randomized controlled trials

This protocol has been prepared in accordance with the Standard Protocol Items: Recommendations for Interventional Trials (SPIRIT) reporting guideline (Supplementary Material 1) [16].

### Design and setting

There are three online survey links, one for each respective population. Each link contains eligibility questions, the consent form, and study information for youth, parents, or adults. Participants will access the online survey corresponding to their respective population to enter the trials and provide implied consent by participating in the survey. Using the concealed allocation code of the intervention platform, SurveyMonkey (surveymonkey.com), participants will select their geographic region. Participants from each geographic region will be randomized to one of two recommendation topics, and then they will be randomized to a PLR format (intervention) or a SLV format (control) of the recommendation (Fig. 1). The SLV is the original PDF guideline developed and published by an organization, such as the World Health Organization, from where the PLR information was extracted. Participants will complete an online survey consisting of Likert-scale questions, multiple-choice questions, open-ended questions, and demographic information. The survey is anonymous.

**Fig. 1 Fig1:**
[figure not shown]
RCT flow diagram

Following completion of the online survey, we will invite participants to take part in an optional qualitative interview that will allow them to reflect on their preference for the PLR or SLV format and help us understand the results of the quantitative survey. Confidentiality will be maintained by storing names and emails on a password-protected device and secure network to which only authorized study personnel have access to. If participants decide to provide their name and email address to participate in the interview, receive the study results, or enter the draw (for a chance to win one out of five $50 CAD gift cards for the adult and parents’ sites, one out of ten $25 CAD gift cards for the youth site), this personal information will not be linked to their survey answers.

This is not a clinical trial; thus, there are no foreseeable harms or health risks from participating. However, there is a possibility that participants may experience distress once they better understand the uncertainty in the underlying evidence, even if the recommendation itself is judged trustworthy. We provide the email address and contact information of the principal investigator and research coordinator. Participants can contact us to report any discomfort or seek further information.

### Participants

Each of the three leading sites will recruit participants from one of the three population groups: adults, parents, or youth. SickKids Research Institute will lead the recruitment of youth, Western University will lead the recruitment of adults, and The University of Alberta will lead the recruitment of parents. Global recruitment efforts will take place via social media. Coordination and oversight of the trials rest with the research team at McMaster University ([name]). Our study is also open for other sites who are interested in participating as active recruitment sites for one or more populations. For example, St. Elizabeth University in Slovakia is joining as an active recruitment site for all three populations, with a commitment to recruit up to 60 participants.

#### Selection criteria

In this study, adults are defined as individuals self-reported to be 21 years of age or older, youth are defined as individuals self-reported to be between the ages of 15 and 24 years [17], and parents are defined as individuals self-reported to be 18 years or above and are a parent or legal guardian of a child under 18 years old. Participants can be from any country. For all three populations, participants will need to be able to read and understand English. We expect variation in the English language proficiency and health literacy level among participants. Therefore, when collecting demographic information, questions related to language proficiency and familiarity with COVID-19 health information will be included to understand the participant’s level of health literacy. We may adjust for these variables in our analysis if needed, although we expect them to be reasonably balanced between the SLV and PLR groups due to randomization.

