#### Recruitment

Each leading site will run recruitment for the different population groups separately yet with similar and overlapping strategies. We will recruit English-speaking (mother tongue or fluent) participants globally through our experienced RecMap investigator team (https://covid19.recmap.org/about), the Cochrane Consumer Network and various Cochrane networks, guideline co-authors who interact with youth (including the international Young Persons’ Advisory Groups), parents, and adult citizens. We plan to run public recruitment campaigns through identified youth, adult, and parent organizations’ social media platforms (e.g., organizations’ accounts on Twitter, Instagram, and Facebook) and newsletters. Each leading site will be responsible for monitoring its own recruitment, though all investigators will support overall recruitment for the trials (e.g., if recruitment falls behind for one of the populations, other sites will help support recruitment for that group). Surveys will be administered through SurveyMonkey, where participants are screened for eligibility prior to allocation. Previous studies suggest that the target recruitment rates for such trials are achievable in less than 3 months, and we will recruit at least 240 participants per group [18–20].

The average survey completion time is estimated to be 15–25 min, based on stakeholder feedback and pilot testing. As suggested by our stakeholders in the preparation of this trial, we will be inviting participants who complete the survey to enter a draw for a chance to win one of five $50 CAD gift cards for the adult and parents’ populations. The youth group will invite youth participants to enter a draw for one of ten gift cards valued at $25 CAD. This is offered as a gesture and appreciation for completing the survey.

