**Fig. 3 Fig3:**
[figure not shown]
Example of a plain language recommendation summary format for adult participants

Through our pre-trial engagement work, we gathered input from youth (via online workshops) and from adult stakeholders (via online meetings) on high-priority COVID-19 topics and on PLR content and format. Input from youth and adult stakeholders allowed us to choose two recommendations for the trials and refine the PLR format. For the parents’ population, the PLRs were refined from collected feedback during online meetings with parent groups.

All PLRs for the trials were developed from the same template and refined using stakeholder feedback. The youth and parent PLRs’ design and formatting are the same, as these groups gave similar feedback, while the adult PLRs are slightly different.

In the trials, we will ask participants to read one format of a recommendation (PLR or SLV) to which they have been randomly allocated and then answer the online survey that takes an average of 15–25 min to complete.

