### Statistical analysis

Only participants who submit a complete good quality survey will be included in the analysis. We will exclude all incomplete, speeding (less than 6 min to completion), and straight-lining responses. Each population’s results will be analyzed separately, and we will explore subgroup effects within each group. These subgroups are the topic of recommendation, health literacy level, and English proficiency level of participants. We will also pool the results across populations and conduct a meta-analysis for our primary outcome of “understanding” and other secondary outcomes. In the final analysis, after pooling the results, we will explore for potential interaction related to the recommendation topic and participants’ health literacy level. We will conduct the analyses using IBM SPSS® (Statistical Package for Social Sciences) version 23.

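### Self-rated COVID-19 familiarity, part of the health-literacy measure, appears to be asked after the allocated format is read, yet is used as a baseline covariate and subgroup

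*Protocol article*

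**What the plan says.** **Timing.** Two things are explicitly placed before allocation. Recruitment states that "participants are screened for eligibility prior to allocation", and Design and setting states that "participants will select their geographic region" before the two randomisation steps. After those steps, Design and setting continues: "Participants will complete an online survey consisting of Likert-scale questions, multiple-choice questions, open-ended questions, and demographic information". Intervention and comparison (text below Fig. 3) says that participants will "read one format of a recommendation (PLR or SLV) to which they have been randomly allocated and then answer the online survey".

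**The items.** Selection criteria says that, when demographic information is collected, "questions related to language proficiency and familiarity with COVID-19 health information will be included to understand the participant’s level of health literacy".

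**Their use.** The same paragraph says "We may adjust for these variables in our analysis if needed" and gives randomisation as the reason to expect reasonable balance between the arms. Statistical analysis adds, for each population, "These subgroups are the topic of recommendation, health literacy level, and English proficiency level of participants". For the pooled analysis it says "we will explore for potential interaction related to the recommendation topic and participants’ health literacy level". English proficiency is not named in the pooled step.

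**The concern.** A covariate or subgroup variable has to be unaffected by the treatment. Randomisation balances what participants bring to the trial. It gives no such guarantee for an answer they give after seeing the allocated material.

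Here the material is a COVID-19 recommendation, shown either as a plain summary or as the original guideline PDF. One of the questions asks how familiar the reader is with COVID-19 health information. A clear text might make a reader feel better informed, and a dense one less so. The opposite is also conceivable, since a plain summary may show readers what they did not know. Either way, part of the format effect would enter the variable used to adjust or split the data.

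Two sets of results are exposed: any adjusted estimate of the format effect, and the health-literacy subgroup and interaction results within and across populations. A conclusion that plain language works better or worse at a given literacy level could then partly reflect question order.

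**Working it through.** The plan gives no figure on this point. The check therefore has two parts: where the items sit, and how much a shift would matter. The shift and all model parameters below are assumptions unless a source is named.

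**1. Order of events**

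| Step | Source | Relative to allocation |
|---|---|---|
| Eligibility screening | Recruitment | before (stated) |
| Region | Design and setting | before (stated) |
| Topic, then format | Randomization | allocation |
| Read the allocated format, then answer the survey | Intervention and comparison | after (stated) |
| Demographic information is part of the survey | Design and setting | after (inferred) |
| Proficiency and familiarity are asked with the demographics | Selection criteria | after (inferred) |

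**2. Adjusted effect on the 0–7 score**

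Inputs:
- True effect of 1 correct answer, the average difference named under Primary outcome.
- Assumed: score SD 1.6; correlation ρ of 0.3 to 0.5 between true ability L and understanding; correlation 0.8 between self-rating and L; the plain-language format raises the self-rating by δ = 0.2 to 0.5 SD.

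Model, with T = 1 for the plain-language arm:
- y = 3.9 + 1.0·T + 1.6·(ρL + √(1−ρ²)·noise)
- R = 0.8·L + 0.6·noise + δT

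Within an arm, var(R) = 0.64 + 0.36 = 1 and cov(y, R) = 1.6 × ρ × 0.8 = 1.28ρ. The slope of y on R is therefore 1.28ρ. Adjustment subtracts this slope times the difference in mean R:

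adjusted effect = 1 − 1.28·ρ·δ

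| δ | ρ | Arithmetic | Adjusted effect |
|---|---|---|---|
| 0 | any | 1 − 0 | 1.00 |
| 0.2 | 0.3 | 1 − 0.077 | 0.92 |
| 0.3 | 0.5 | 1 − 0.192 | 0.81 |
| 0.5 | 0.5 | 1 − 0.320 | 0.68 |

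A simulation with 4 million participants per scenario gave the same values, and the unadjusted difference stayed at 1.00 throughout. If the format lowers the self-rating instead, the sign reverses: δ = −0.2 with ρ = 0.3 gives 1 + 0.077 = 1.08.

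With a median split on R, the low and high effects were about 0.95 and 0.95 (δ = 0.2, ρ = 0.3) and 0.80 and 0.80 (δ = 0.5, ρ = 0.5). A shift of equal size for everyone thus lowers both halves and leaves the contrast between them almost intact.

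**3. Subgroup contrast when only some readers shift**

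Inputs:
- Control rate 60% and true risk difference 0.15 (75% minus 60%, Sample size calculation).
- Assumed: half the readers are truly low in literacy, and the true difference is 0.15 in both strata.

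*Shift unrelated to the answers.* Take a 20-point literacy gap, so the control rates are 0.50 and 0.70 and the plain-language rates 0.65 and 0.85. Suppose 20% of low-literacy plain-language readers report high.
- Reported-high rate in that arm: (0.5 × 0.85 + 0.1 × 0.65)/0.6 = 0.817, so the difference is 0.117.
- Reported-low difference: 0.65 − 0.50 = 0.150.
- False interaction: 0.117 − 0.150 = −0.033.
- Adjusted difference, with weights n₁n₀/(n₁+n₀) of 0.273 and 0.222: (0.273 × 0.117 + 0.222 × 0.150)/0.495 = 0.132.

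Over literacy gaps of 10 to 30 points and shifts of 10% to 30%, the adjusted difference is 0.110 to 0.145 and the false interaction −0.01 to −0.07.

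*Shift only among low-literacy plain-language readers who answered correctly.* Keep the 20-point gap and let 20% of these readers report high. The share that moves is 0.5 × 0.65 × 0.2 = 0.065.
- High: (0.425 + 0.065)/0.565 − 0.70 = 0.167.
- Low: (0.325 − 0.065)/0.435 − 0.50 = 0.098.
- False interaction: +0.07.

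Over shifts of 10% to 30%, the false interaction is +0.03 to +0.11 and the adjusted difference 0.125 to 0.143.

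With no shift, every one of these quantities equals its true value.

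**The case against.** **The order is inferred.** No sentence says that these items follow the format. The sentence in Design and setting lists question types rather than a sequence, so the last place of demographic information in it proves nothing. The word survey also covers the whole link, including the eligibility pages. Descriptive analysis calls the participant characteristics baseline, and neither Fig. 1 nor the questionnaire is shown. All of this stands. What remains is that the allocated format is read before the survey is answered, and that only eligibility and region are explicitly put ahead of allocation.

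**A reader might infer that the primary result is biased.** The documents do not support that. Inferential analysis plans an unadjusted chi-square test and risk difference for understanding, which uses none of these variables. Adjustment is optional and the subgroup analyses are exploratory.

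**A reader might also infer that the subgroup results become uninterpretable.** That goes too far. A uniform shift leaves the low-versus-high contrast nearly intact. Distortion of the contrast needs a shift that differs between readers, and its sign depends on who shifts.

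**English proficiency is a largely stable trait,** and Recruitment aims for mother-tongue or fluent speakers. Reading one document is unlikely to change that answer much. The concern rests mainly on familiarity.

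**No shift is documented.** This is correct: its existence and size are assumptions.

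**Conclusion.** The point holds as a design weakness in secondary analyses. On the natural reading, self-rated familiarity is collected after exposure and then given roles that are valid only for a pre-exposure measure. Randomisation cannot be relied on to balance it.

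The size depends wholly on an assumed shift. For 0.2 to 0.5 SD in favour of the plain-language format, an adjusted effect of 1.00 correct answer becomes about 0.92 to 0.68, and a shift the other way would inflate it. A false health-literacy interaction of either sign is possible if readers shift unequally. Such results could not safely be read as baseline effect modification.

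**What to change.** - State in the protocol when the proficiency and familiarity questions are asked. If they already precede allocation, that sentence is enough and nothing else needs to change.
- If they follow the format, move them to the existing eligibility and region page, ahead of randomisation. Use only values collected there for adjustment and for the subgroup and interaction analyses.
- For responses already collected after exposure (Trial status gives a recruitment start of May 26, 2022), leave familiarity and health literacy out of adjusted analyses of understanding. Report their subgroup and interaction results as descriptive and based on a post-exposure measure.

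**Cost.** No new items are needed. Changing the order during recruitment gives each population two question orders and leaves fewer participants with pre-allocation values for the subgroups. It also adds a very small risk that people leave before randomisation, which does not bias the comparison between arms.
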